### Intervention delivery

The intervention will be delivered via the *PATHS* website [64] (see Fig. 2 for screenshot examples). Participants in all conditions will log-in to the web-based intervention using their email address and password created while going through the eligibility assessment process. Participants in all conditions will have access to the *Library* in the form of brief clear-language descriptions of physical activity recommendations and information on the importance of physical activity. Given research demonstrating that providing information about health behaviour alone is not sufficient to change behaviour [65], but also recognising the need to provide a rationale for engaging in the website and to ensure that information is controlled across conditions, all study participants will have access to the *Library*.

**Fig. 2 Fig2:**
[figure not shown]
*PATHS* study – intervention screenshots – content examples

All participants will also have access to *Frequently Asked Questions* page, a sub-section of the website about practicalities of its use (e.g., how to change their password, basic features, tips on navigating through the website). This sub-section of the website has been designed based on piloting previous similar website [66]. Participants will be able to contact an intervention facilitator if they have any additional questions about participating in the study. There will also be an *About* page available – a sub-section of the website that will (1) explain the reasons why the intervention was developed and (2) introduce the *PATHS* study research team to add credibility. A *Frequently Asked Questions* page and an *About* page, also developed from previous investigations piloting the platform, will be slightly different for each intervention condition to account for the differences between conditions.

Participants allocated to the three intervention groups will have access to additional intervention features. Each fortnight, they will be prompted via email to access the website and to answer short online surveys and receive tailored feedback based on the information provided in their responses. Depending on their group allocation (Tables 1 and 2), participants will receive feedback aimed at promoting motivation (motivation group), motivation and self-regulation (self-regulation group), or motivation, self-regulation and prompts for actions (habit group). Information pertinent to the participant’s condition will be delivered via personally-tailored messages presented as text on a webpage accompanied by appropriate pictures and graphs with tailored information (e.g., graphs showing participant’s change in physical activity or weight throughout the intervention). The intervention will include six consecutive sessions that will be presented fortnightly for three consecutive months.

**Table 1 Tab1:** Intervention content for *PATHS* study **-** overview

Session number	Motivation condition	Motivation + self-regulation condition	Motivation + self-regulation + habit condition
1	Motivation and self-efficacy	Motivation, self-efficacy and self-monitoring	Motivation, self-efficacy, self-monitoring and habit development
2	Goal setting	Goal setting and action planning	Goal setting, action planning and forming positive habits
3	Self-efficacy, barriers identification and staying motivated when facing barriers	Self-efficacy, barrier identification and staying motivated and self-regulating when facing barriers	Self-efficacy, barriers identification and staying motivated, self-regulating in face of barriers and recognising cues to action
4	Social support and motivation	Social support and motivation, and self-monitoring with others	Social support and motivation, self-monitoring and forming activity routines with others
5	Experiencing barriers to being active and staying motivated	Experiencing barriers to being active and staying motivated; relapse prevention	Experiencing barriers to being active and staying motivated; reasons for falling back into bad habits; relapse prevention
6	Summary: staying motivated	Summary: staying motivated and self-regulating	Summary: staying motivated, self-regulating and maintaining habits

**Table 2 Tab2:** Variables assessed, feedback topics, BCTs and constructs targeted in each session (Motivation + Self-regulation + Habit condition combined)

Session number	Session topic	Variables assessed (number of questions)	Feedback topics (number of permutations, i.e. possible variations of the response)	BCTs included^a^	Constructs targeted
1	Motivation, self-efficacy, self-monitoring and habit development	- Demographics (5) - Physical activity (10) - PA goal (1; 5 options) - PA self-efficacy (1; Not at all certain/ Moderately certain / Highly certain) - Preference for PA routine (1; 5 options) - Habit Automaticity Index (4 questions) - Feedback on the session after tailored advice (1)	- Introduction based on the condition (3) - Motivation: Physical activity guideline according to the selected main motivation (7) - Self-regulation: Feedback on current physical activity level in relation to the main motivation chosen, presented with graph (87) - Habit: Developing habits based on preferred PA, need for behavioural repetition (5) - Habit: Recognising prompts in relation to the habit automaticity level (3) - Self-regulation: Setting a goal for the next two weeks based on self-efficacy levels; goal is predetermined (9) - Conclusion based on the condition and main motivation (15)	1.1. Goal setting (behaviour) 2.2. Feedback on behaviour 5.1. Information about health consequences 5.6. Information about emotional consequences 7.1. Prompts/cues 8.3. Habit formation 15.1. Verbal persuasion about capability	Knowledge, goals, intrinsic motivation, autonomy, self-efficacy, intentions, outcome expectations, cues and habits
2	Goal setting, action planning and forming positive habits	- Physical activity (10) - Weight (1) - Goal setting (2) - Open questions about long and short term goals (2) - Habits and prompts (2) - Action planning phrased with/without references to habit – open answers (5) - Feedback on the session after tailored advice (1)	- Welcome based on the condition (3) - Self-regulation: PA guidance refresher based on the main goal (5) - Physical activity progress feedback (27) - Motivation: Long and short term goals with SMART goals principles (4) - Habit: Feedback on developing habits and noticing prompts (4) - Self-regulation: Action plan (1) - Habit: Action plan with reference to behaviour repetition in a stable context (1) - Conclusion based on the condition (3)	1.1 Goal setting (behaviour) 1.3. Goal setting (outcome) 1.4. Action planning 2.2. Feedback on behaviour 7.1. Prompts/cues 8.3. Habit formation	Knowledge, self-efficacy, attitudes, perceived behavioural control, goals, intentions, cues and habits
3	Self-efficacy, barriers identification and staying motivated, self-regulating in face of barriers and recognising cues to action	- Physical activity (10) - Weight (1) - Coping self-efficacy (6) - Action plan completed (1) - Main prompts (1; 5 options) - Action plan evaluated open answers (5) - Confidence to recognise prompts (1) - Feedback on the session after tailored advice (1)	- Welcome based on the condition and prompts recognised for Habit group (9) - Motivation: Boosting your confidence and staying motivated based on identified barriers (6) - Self-regulation: Physical activity progress feedback includes graphs (52) - Habit: Feedback on developing habits (6) - Habit: Noticing prompts (5) - Self-regulation: Action plan (1) - Habit: Action plan with reference to behaviour repetition in a stable context (1) - Conclusion based on the condition (3)	1.4. Action planning 1.5. Review behaviour goal(s) 1.6. Discrepancy between current behaviour and goal 5.4. Monitoring of emotional consequences^b^ 5.5. Anticipated regret 5.6. Information about emotional consequences 7.1. Prompts/cues 8.3. Habit formation	Knowledge, self-efficacy, attitudes, perceived behavioural control, coping self-efficacy, goals, intentions, emotions, cues and habits
4	Social support and motivation, self-monitoring and forming activity routines with others	- Physical activity (10) - Weight (1) - Positive social support (3) - Negative social support (3) - Influence of others (1) - Feedback on the session after tailored advice (1)	- Welcome based on the condition (3) - Self-regulation: Physical activity progress feedback (52) - Motivation: Positive influence of others and dyadic plans (20) - Self-regulation: Positive influence of others and dyadic plans (20) - Habit: Positive influence of others and dyadic routines (20) - Negative influence of others and staying motivated when others are not supportive (20) - Encouraging other people to be active (2) - Conclusion based on the condition (3)	1.5. Review behaviour goal(s) 1.6. Discrepancy between current behaviour and goal 1.7. Review outcome goal(s) 3.2. Social support (practical) 3.3. Social support (emotional) 6.3. Information about others’ approval 10.9. Self-reward 12.2. Restructuring the social environment	Self-efficacy, knowledge, goals, intrinsic motivation, autonomy, social support, subjective norm, habit, routine
5	Experiencing barriers to being active and staying motivated; reasons for falling back into bad habits; relapse prevention	- Physical activity (10) - Weight (1) - Behavioural barriers (2) - Open question re-evaluating short term goal for PATHS (1) - Habit development (2) - Feedback on the session after tailored advice (1)	- Welcome based on the condition (3) - Self-regulation: Physical activity progress feedback (52) - Habit: Maintaining positive habits – coping planning (4) - Motivation: Relapse prevention based on the main barrier selected with an emphasis on staying motivated (10) - Self-regulation: Relapse prevention based on the main barrier selected with an emphasis on staying motivated and self-regulating (10) - Habit: Relapse prevention based on the main barrier selected with an emphasis on staying motivated/self-regulating and maintaining positive habits (10) - Conclusion based on the condition (3)	1.2. Problem solving 1.7. Review outcome goal(s) 7.3. Reduce prompts/cues 8.2. Behaviour substitution 8.4. Habit reversal 11.2. Reducing negative emotions 12.3. Avoidance/ reducing exposure to cues for the behaviour	Self-efficacy, intrinsic motivation, goals, intentions, knowledge, attitudes, perceived behavioural control, emotions, self-regulation, habits, cues-to-action, behavioural barriers
6	Summary: staying motivated, self-regulating and maintaining habits	- Physical activity (10) - Weight (1) - Habit Automaticity Index (4 questions) - Feedback on the session after tailored advice (1)	- Welcome based on the condition (3) - Self-regulation: Physical activity progress feedback with graph (52) - Self-regulation: Weight changes throughout the program with graph (16) - Motivation: Tips to stay motivated (1) - Self-regulation: Tips to stay motivated and to self-regulate PA (1) - Habit: Tips to stay motivated and to self-regulate PA and to follow newly developed routines (1) - Motivation: Success stories from other hospital employees who increased their PA (1) - Conclusion based on the condition (3)	2.2. Feedback on behaviour 2.7. Feedback on outcome (s) of behaviour 5.1. Information about health consequences 5.6. Information about emotional consequences 6.3. Information about others’ approval 8.1. Behavioural practice/rehearsal 9.2. Pros and cons	Self-efficacy, Intrinsic motivation, Autonomous Motivation, Intention to maintain the behaviour, Habit

^a^ Names and numbers according to V1 Behaviour Change Taxonomy: Michie, Susan, et al. “The behavior change technique taxonomy (v1) of 93 hierarchically clustered techniques: building an international consensus for the reporting of behavior change interventions.” Annals of behavioral medicine 46.1 (2013): 81–95.

^b^ Use of this BCT will depend on the option selected by the participants.

Numbers in brackets indicate the possible number of feedback permutations

Each fortnight, participants will be provided with a new session including a recap of the messages from the previous two weeks along with new personally-relevant content and tailored feedback. If participants do not complete the session on time, they will be able to do so when they next login. Each session will end with a pop-up notification asking users to use a star rating system (*What did you think of this feedback?* 0 to 5 stars) and a qualitative *feedback box* to receive open-ended comments relating to each session content (*Why did you rate it this way?* [optional]).

During each intervention session, participants will receive personally-relevant content incorporating BCTs relevant to their allocated intervention condition (Table 2). To generate the content-specific information, participants will be asked about their physical activity during the previous week at the beginning of each intervention session (including their low, moderate and high intensity physical activity, and resistance training, specifying number and length of sessions). They will also be asked questions regarding the psychological determinants of physical activity, physical resources, and social and environmental factors relevant to the condition to which they are allocated. For example, during the session on goal setting, participants allocated to the Motivation condition will receive information which prompts them to form activity goals and to stay motivated to achieve them. Participants allocated to the Self-regulation condition will also receive suggestions how to monitor and self-regulate towards the goal (action planning, coping planning). Participants assigned to the Habit condition will also receive information on the importance of repetition of the same activity in the same context to develop habits.

The platform uses if-then algorithms to provide tailored feedback based on the participant’s responses. The feedback will be drawn from a database of messages incorporating feedback combinations tailored to the participant’s condition and responses to prompts for information on the website. The platform will store participants’ responses for each session, permitting tailoring of the intervention to the responses from the current session, as well as to responses from previously completed surveys. For instance, graphs displayed to the participants will include changes in physical activity throughout the intervention.

In addition, all groups, with the exception of the control group, will receive weekly text messages sent at the same time each week to provide further condition- and session-relevant feedback based on their most recently completed session and including a short summary of key points. There will be three introduction messages and each session has two session specific text messages, followed by a final concluding message. Participants will also receive regular fortnightly reminders to login to the intervention website when a new session is available sent via email. Up to three reminders will be sent per session (one every four days).

### Measures

Table 3 describes measures that will be taken during the study, specifying the type of outcome assessed, the measurement tool used, the number of questions included, and the time points when the measures will be administered.

**Table 3 Tab3:** Measures taken at Time 1 and Time 2 and outcomes assessed

Measurement tool	Reference	Number of items		Outcome
		Time 1	Time 2	
		(baseline)	(3 months)	
Survey measures				
Confirmation of eligibility to participate in the study	N/A	8	-	Eligibility
Physical Activity Readiness Questionnaire (PAR-Q)	[45]	8	-	Readiness to undertake PA
Demographics	Commonly used items	14	6	Age, sex, marital status, ethnicity, education, weight, height, house income, postcode
International Physical Activity Questionnaire (short version)	[68, 69]	7	7	Physical Activity
Job-related physical activity	From: International Physical Activity Questionnaire (long version) [68]	8	8	Job-related physical activity
The Pittsburgh Sleep Quality Index (PSQI)	[70]	9	9	Sleep
Theory-relevant determinants of physical activity	Individual items taken from different questionnaires	30	30	Motivation, attitudes towards regular physical activity, outcome expectations, perceived behavioural control, subjective norms, intentions, barriers self-efficacy, action planning and coping planning, self-efficacy, goal facilitation and goal conflict
Self-report behavioural automaticity index	[77]	8	8	Behaviour automaticity
Personal Need for Structure Scale	[78]	12	-	Personal Need for Structure
Physical activity intentions	[72]	3	3	Physical Activity Intentions
Depression Anxiety Stress Scale 21 (DASS 21)	[79]	21	21	Depression, Anxiety, Stress
SF 12	[80]	12	12	Quality of life
Physical Activity Neighbourhood Environment Survey (PANES)	[81]	17	-	Perceptions of the environment in relation to PA
Internet use and access to the intervention	Items developed for this study	-	4	Internet use and access to the intervention
Internet self-efficacy scale	[83]	9	-	Internet self-efficacy
SUS and satisfaction	[82]	-	16	SUS and satisfaction
Physical advice acceptability	[66]	-	15	Physical advice acceptability
Delivery mode usability	[66]	-	5	Delivery mode usability
Usefulness questions	[66]	-	5	Intervention usefulness
Format-related questions	[66]	-	9	Format
Total items		158	158	
Outcome measures and moderators				
Physical activity objectively measured with GENEActiv	[47, 67]	✓	✓	Objectively measured physical activity
Sleep objectively measured with GENEActiv	[47]	Optional	Optional	Objectively measured sleep
Planning skill task	[90]	✓	-	Planning skills/ability

#### Physical activity

The primary outcome will be measured physical activity over a one-week period prior to the intervention (Time 1) and for a further week immediately post-intervention at the three-month follow-up occasion (Time 2) using accelerometers (GENEActiv Ltd.) [47, 67]. Participants will be asked to wear the unit continuously for the seven day period on the non-dominant upper arm to comply with hospital hygiene regulations. The GENEActiv device is water proof and participants will be informed that they are free to choose whether to wear it while swimming, showering, or sleeping. Data will be collected at 60 Hz epoch frequency. Step counts will be derived from the acceleration data using open-source macros and they will be used as proxy for physical activity [47]. Participants will be supplied with a band specifically designed to fasten the monitor to the upper arm.

Secondary outcomes will be assessed at baseline (Time 1) and post-intervention (Time 2), and will include subjective measures of physical activity, sitting time, sleep, depression, anxiety, stress, quality of life, theory-derived correlates of physical activity and self-reported weight. Demographics, perceived neighbourhood environment, personal need for structure, internet self-efficacy, and planning skills/ability will be assessed at baseline (Time 1) only. Secondary outcomes assessed only at the post-intervention stage (Time 2) will include measures of intervention accessibility, usefulness and satisfaction with the intervention, as well as acceptability of the advice provided. Participants’ website usage (e.g., time spent on pages with specific intervention content, number of website visits) will be assessed throughout the study using Google Analytics.

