## Methods

### Participants

Full- and part-time hospital staff including midwives, clinical nurse managers, clinical nurses, registered nurses, enrolled nurses, and patient care assistants will be eligible to participate in the *PATHS* study. Participants will be recruited from hospitals in Perth, Western Australia. Staff working in shift and non-shift patterns will be eligible to participate. No restrictions will be placed on the type of contract and number of hours worked. Participants are eligible if they fail to meet the recommended weekly level of 150 min of moderate intensity physical activity because the intervention is designed for people who fail to meet this level.

Individuals who self-report a physical condition or impairment preventing them from being physically active will be excluded from the study. They will be screened using the Physical Activity Readiness Questionnaire (PAR-Q) prior to study consent [45]. However, individuals who are not eligible to participate in the study based on PAR-Q measures can still consult their GP to obtain approval. Hospital employees who do not have a mobile phone that allows them to receive text messages, who do not have access to internet on their mobile phone, computer or tablet outside of work, who are already meeting weekly recommended levels of physical activity or are currently participating in another physical activity program (e.g., a structured weight loss program, regular meetings with personal trainer or coach) will be excluded.

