### Procedure

After screening, eligible participants will be contacted by a study researcher who will arrange a one-on-one meeting (Figure 1, CONSORT flow diagram). During the meeting, the participant will receive a detailed explanation of the study, and its requirements and expectations from the researcher. They will also be provided with an information sheet providing the same information and outlining their rights to confidentiality and to withdraw from the study at any stage without consequence. Once the participant has had the opportunity to confirm their understanding of the project and have any questions answered, they will be asked to sign an informed consent form.

A study researcher will set up and initiate a GENEActiv activity monitor [47] for each participant, including programming the participant’s code number, date of birth, height, and handedness. Each monitor will be programmed to start collecting data from set up. Study participants will be required to wear the monitor on their non-dominant upper arm and will be provided with detailed instructions on how to wear the device. Participants will be instructed to wear it continuously throughout day and night for one week after the first meeting.

Eight days later, participants will meet with the researcher again to return the activity monitor. The study facilitator will check if sufficient data have been collected by the device (i.e., at least five days of wear with a minimum 16 h wear per day) [48]. If the participant fails to wear the activity monitor for the minimum time specified, they will be asked to wear it again for another seven days. At this second meeting, participants will also be asked to complete web-based baseline questionnaires using a provided tablet (Time 1).

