#### Self-regulation condition

Participants assigned to the self-regulation condition will receive the content from the motivation condition along with content promoting self-regulation. Specifically, participants will be encouraged to set outcome-specific goals [56] and to self-monitor their progress towards these goals by monitoring how much time they spent doing physical activity. They will also be prompted to form action and coping plans [57], specifying when, where and how they will perform their physical activities, and identifying barriers to their physical activity participation and how they might overcome them. Participants will be encouraged to specifically focus on self-monitoring in high risk situations [58], such as when they are tired or stressed and their capacity for self-regulation is most likely to be compromised [59, 60]. Participants will also receive information on managing multiple goals [61] and self-regulating the situation when competing activities arise (e.g., the desire to be active and healthy conflicts with other situational options such as watching TV and resting).

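### Participants are enrolled on moderate-intensity minutes and counselled on time and intensity, but the only objective activity outcome is a step count that carries no intensity and includes on-shift walking, which adds avoidable noise

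*Protocol article*

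**What the plan says.** All places are in the protocol article, under Methods unless stated.

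- **Entry (Participants).** "Participants are eligible if they fail to meet the recommended weekly level of 150 min of moderate intensity physical activity". The same section says: "Staff working in shift and non-shift patterns will be eligible to participate", and places no limit on contract type or hours.
- **Counselling (Intervention delivery; Self-regulation condition).** Each session asks about the past week's activity, "including their low, moderate and high intensity physical activity, and resistance training, specifying number and length of sessions". Self-monitoring is by "monitoring how much time they spent doing physical activity".
- **Primary outcome (Measures, Physical activity).** "Step counts will be derived from the acceleration data using open-source macros and they will be used as proxy for physical activity". The other activity measures listed are self-reported.
- **Wear (same section; Procedure).** "Participants will be asked to wear the unit continuously for the seven day period on the non-dominant upper arm", a site chosen because of hospital hygiene rules. Participants are "free to choose whether to wear it while swimming, showering, or sleeping". A recording is sufficient with "at least five days of wear with a minimum 16 h wear per day"; work days and days off are not distinguished.
- **Work information (Demographics; Table 3).** Hours and days worked per week, shift type and three-month absenteeism are recorded. An eight-item self-reported job-activity module is given at both time points.
- **Model (Study analysis).** A mixed model of condition by time, with nesting within hospital. No work-related term is named.

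**The concern.** Two separate things are at stake.

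The first is construct match. The deficit that brings someone into the trial is defined by intensity and duration, and the feedback speaks in those terms. A step count sees neither. Someone who takes up cycling (one of the Background's examples of moderate activity) or resistance training could pass the entry threshold with little change in steps. Equally, steps could rise with no change in moderate-intensity time.

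The second is precision. Each time point rests on a single week in nurses, midwives and care assistants. If shifts involve more walking than days off, a week with more shifts gives more steps. A change in roster between the two weeks then appears as a change in the primary outcome without any change in behaviour.

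**Working it through.** **No plan figure to reproduce.** The article gives no step SD, no difference between work days and days off, no roster spread and no share of activity outside walking or running. The size of the construct mismatch cannot be computed. The roster noise can only be illustrated.

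**Is on-shift walking in the outcome?** The article does not say so outright. It follows from continuous wear, from a wear site chosen to satisfy hospital hygiene rules, and from the absence of any rule removing work time.

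**Inputs from the article.** Seven days of wear requested; five valid days at minimum; two time points; 134 evaluable participants (Sample size).

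**Assumed inputs.**
- Work days exceed days off by D = 4,000 steps (range 2,000–6,000).
- SD of mean daily steps 3,000 at each time; baseline–follow-up correlation 0.5.
- The number of work days in the window has SD 1 at each time, independent between the two weeks.

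**Formulas.** A condition-by-time comparison over two time points is in effect a comparison of mean changes.
- SD of change = 3,000 × √(2 × (1 − 0.5)) = 3,000, so the variance is 9,000,000.
- One day switching between off and work moves a mean over k days by D/k.
- Roster share of change variance = 2 × (D/k)² / 9,000,000.
- If adjustment removed all of it, the gain would equal multiplying the sample by 1/(1 − share).

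| Days k | D | D/k | Share | 1/(1 − share) |
|---|---|---|---|---|
| 7 | 2,000 | 286 | 1.8% | 1.02 |
| 7 | 4,000 | 571 | 7.3% | 1.08 |
| 7 | 6,000 | 857 | 16.3% | 1.20 |
| 5 | 2,000 | 400 | 3.6% | 1.04 |
| 5 | 4,000 | 800 | 14.2% | 1.17 |
| 5 | 6,000 | 1,200 | 32.0% | 1.47 |

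**In participants.** At seven days the central case is worth about 134 × 0.078 ≈ 10 more evaluable participants. At the five-day minimum it is about 134 × 0.166 ≈ 22.

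**Sensitivity to independence.** If a person's work-day counts in the two weeks correlate at r, the share is multiplied by (1 − r). At r = 0.5 the central shares fall to about 3.6% (seven days) and 7.1% (five days).

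**The case against.** **Step-based activity is well represented.** Walking, running and football are among the Background's own examples, and all produce steps. No session prescribes an activity type; resistance training appears as something asked about. A reader might infer that much of the promoted activity cannot register. The article does not support that, because it gives no share of non-step activity. What stands is narrower: some promoted activity registers poorly, and intensity does not register at all.

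**Roster variation is not bias.** Individuals are randomised, so roster changes balance between arms in expectation, and the baseline week absorbs stable differences in working pattern. A reader might infer that rosters could create or hide a treatment effect systematically; that does not follow. What remains is the week-to-week part, which is noise.

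**Work is measured.** Shift type and job-related activity are collected, and the questionnaires are completed when the monitor is returned. This is fair, but neither item says which monitored days were shifts, and neither is named in the model.

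**Covariates and derived outcomes belong in an analysis plan.** This is true of the model terms. It is not true of the outcome metric, which the article fixes, or of the rostered-day record, which has to be collected at the visits.

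**The magnitude can be made to look larger than it is.** It is tempting to set 800 steps (one day switching in a five-day window) against a target effect of 0.28 × 3,000 = 840. The first is one person's shift and the second a difference between group means, so they are not comparable. The five-day window is also the minimum, not the expected case.

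**Walking at work can be a real effect.** The intervention is set in the workplace, so on-shift steps should not be discarded. This argues for keeping total steps as primary and reporting off-shift steps beside them.

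**An intensity measure may not solve everything.** Nothing in the article shows that upper-arm acceleration captures cycling or resistance training well. It addresses the intensity mismatch, and the other only in part or not at all.

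**Conclusion.** The point holds as a fixable weakness in construct match and precision; it does not invalidate the primary outcome. Entry and counselling are in intensity and time, while the sole objective activity outcome is blind to intensity. On-shift walking enters it with nothing linking steps to rostered days.

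The avoidable noise is about 7% (2–16%) of change-score variance over seven days and 14% (4–32%) at five, and lower if rosters correlate between weeks. These figures rest wholly on the assumed step difference, SD, correlation and roster spread. Treating all of it as recoverable further assumes a similar work-day increment across participants. The loss from activity that steps register poorly is real in direction but cannot be sized from the article.

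**What to change.** 1. Keep step count as the primary outcome.
2. Name as first secondary outcome an intensity-based measure from the same GENEActiv recordings: time at moderate or higher intensity, or mean acceleration if no cut-point for the upper arm is accepted. Making it co-primary is not recommended, since that would raise a multiplicity question for a limited gain.
3. At each monitor-return visit, record which monitored days were rostered shifts. Record rostered rather than attended days, because absenteeism is itself an outcome.
4. Include the number of rostered days, or day-level status, as a covariate in the step model, and report off-shift steps as a supportive analysis.

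The cost is one question at two existing visits, reprocessing of data already collected, one covariate and one more secondary outcome to report. The roster question is the urgent part: nothing else the article lists would allow those days to be identified at analysis.
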